### Outcomes

**Table Taba:** 

Primary outcome	Exploratory outcomes
Major Depression Inventory (MDI)	Pattern of dropouts and withdrawals from the study Safety, side effect and compliance to study medication Anxiety and depression measured by the Hospital Anxiety and Depression Scale (HADS) Sleep and circadian outcomes measured by actigraphy Subjective sleep quality measured by the Pittsburgh Sleep Quality Index (PSQI) Sleep diary Sleep, pain, anxiety, fatigue and general wellbeing measured by visual analog scales (VAS) Blood samples – Circadian clock gene analysis

### Primary outcome

The MDI is a self-rating scale with 12 questions. It has been extensively used in a Danish population [47] and is also thoroughly validated [48]. The questions cover the ten ICD-10 symptoms for depression, which are identical to the *Diagnostic and Statistical Manual of Mental Disorders, 4th edition* (DSM-IV) major depression diagnostic criteria except for one symptom, low self-esteem (question 4), which in DSM-IV is incorporated into a question about guilt (question 5).

The MDI holds a double function. It can be used as a diagnostic tool which, via an algorithm, can be transformed into the DSM-IV or ICD-10 categories of “mild,” “moderate,” or “severe” depression. The tool has been found to have satisfactory sensitivity and specificity with regard to the diagnosis of depression according to both the ICD-10 and DSM-IV [49]. The MDI can also be used as a rating scale, which can grade the severity of depression and this has been found to have an acceptable correlation with the Hamilton Depression Scale (HAM-D) [48].

For the purpose of the current study, the MDI will be used as a diagnostic tool at baseline with regard to the eligibility (inclusion/exclusion criteria) of the participants. Mild depression excludes participation and, as a diagnostic tool, mild depression is the presence of two core symptoms and two accompanying symptoms of depression. During the study, the MDI will be used as a rating scale to evaluate the severity and development of depressive symptoms. As a rating scale, a total MDI score (0–50 points) of 21 to 25 points corresponds to a mild depression, of 26 to 30 a moderate depression and above 31 points constitutes a severe depression. Incident depressive symptoms, defined as MDI score ≥21 any time after baseline MDI, is the primary outcome assessed using the MDI as a rating scale. Timing of outcome assessment can be seen in the SPIRIT figure (Fig. 3).

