**Methods/design:**

“The effect of MElatonin and Depressive symptoms, Anxiety, CIrcadian and Sleep disturbances in patients after acute coronary syndrome” trial (MEDACIS) is a multicenter, double-blinded, placebo-controlled, randomized clinical trial. A total of 240 patients with ACS and no depressive symptoms will be included in the trial for treatment with either 25 mg melatonin or placebo for a 12-week period. Development and severity of depressive symptoms will be evaluated using Major Depression Inventory every 2 weeks with the purpose of investigating the potential preventive effect of melatonin on depressive symptoms.

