### Eligibility criteria

Inclusion criteriaPatients should be admitted to a coronary care unit for ACS [46], and should be enrolled at the latest 4 weeks after the primary ACSParticipants should be aged 18 years or olderNo sign of current depression on the Major Depression Inventory (MDI) used as a diagnostic tool at the point of enrollmentParticipants must sign an Informed Consent Form.Premenopausal women (defined as no menstruation during the last 12 months) should have a negative pregnancy test. Furthermore, women of reproductive age should use reliable birth control (intrauterine devices, hormonal contraceptives including oral pills, patches, vaginal rings, and injections) during the entire trial period

Exclusion criteriaKnown allergic reaction to melatoninOngoing or previous pharmacologically treated depression or bipolar disorderNo dementia as determined by a Mini Mental State Examination (MMSE) score <24 is allowedAt the point of inclusion no participation in other pharmacological intervention trials is allowedNo participants with a diagnosis of Rotor syndrome or Dubin-Johnson syndrome, epilepsy, sleep apnea syndrome, systemic lupus erythematosus (SLE), rheumatoid arthritis (RA) or multiple sclerosis are allowedSevere liver disease, defined as transaminases above three times normal levels, and severe kidney disease defined as an eGRF under 40 ml/minChronic hypnotic treatment previous to the ACSKnown sleep disorder (e.g., insomnia, restless legs, etc.)Work involving nightshiftsDaily alcohol consumption above 5 units of alcohol (1 unit = 12 g alcohol)Predictable poor compliance (not speaking fluent Danish)Pregnant or breastfeeding womenSevere, life-threatening medical condition that implies that the patient cannot participate in the study course (e.g., cancer, stroke)Indication for coronary artery bypass graft (CABG)

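### Entry is judged by the MDI symptom algorithm but the incident endpoint by a total score of 21 or more, so a patient already at 21 or more can enter and be counted as a new case without any change

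*Protocol article*

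**What the plan says.** In the protocol article, Eligibility criteria asks that there be no "sign of current depression on the Major Depression Inventory (MDI) used as a diagnostic tool" at enrolment. Primary outcome confirms that "the MDI will be used as a diagnostic tool at baseline with regard to the eligibility (inclusion/exclusion criteria) of the participants" and gives the excluding state: "Mild depression excludes participation and, as a diagnostic tool, mild depression is the presence of two core symptoms and two accompanying symptoms of depression". That is a rule about the pattern of symptoms. It sets no ceiling on the total.

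After baseline the instrument changes mode: "During the study, the MDI will be used as a rating scale to evaluate the severity and development of depressive symptoms". On that scale, "a total MDI score (0–50 points) of 21 to 25 points corresponds to a mild depression". The endpoint follows: "Incident depressive symptoms, defined as MDI score ≥21 any time after baseline MDI, is the primary outcome assessed using the MDI as a rating scale".

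Statistics repeats the threshold of 21 in the null hypothesis, which concerns the number of participants who develop depressive symptoms. It uses the same threshold for the log-rank and Cox analyses and defines the intention-to-treat population as every randomised patient. Nowhere does the article require a baseline total below 21 for a case to count as new, or remove patients at 21 or more from the risk set. The abstract's Methods/design paragraph describes the population thus: "A total of 240 patients with ACS and no depressive symptoms will be included".

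**The concern.** An incident event needs a patient who was free of the condition at the start. Here freedom from the condition is checked by one rule and its onset by another, and the two are not equivalent. Under Primary outcome, mild depression bars entry and a total of 21 to 25 is mild depression, yet a patient in that band can be eligible.

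Such a patient, if unchanged, becomes an event at the first two-weekly MDI. In the binary analysis this is a case that began before treatment. In the log-rank and Cox analyses it is an event at the first assessment. For a prevention trial the result is an endpoint that is partly prevalent, an effect that tends towards no difference, and some loss of power.

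**Working it through.** **1. The plan's own figure.** Inputs from Sample size: 31% v 15.5%, two-sided 5%, power 0.80. The mean rate is p̄ = 0.2325.

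n = [1.96·√(2p̄(1−p̄)) + 0.8416·√(p₁(1−p₁)+p₂(1−p₂))]² / (p₁−p₂)²
= [1.96×0.5974 + 0.8416×0.5873]² / 0.155²
= 2.7726 / 0.024025 = 115.4, so 116 per arm.

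This matches the stated 116. At the planned 120 per arm the same formula gives power of 81.5%. The sample-size figure is not at issue.

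**2. Can an eligible patient score 21 or more?** Primary outcome gives ten symptoms and a total of 0 to 50, from which up to 5 points per symptom is inferred. Take one core symptom at 5, four accompanying symptoms at 4 and all others at 0: 5 + 4×4 = 21. Only one core symptom can be present, whatever item cut-off the algorithm uses (the article gives none), so the two-core requirement is not met. The patient is eligible and already at the endpoint threshold.

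**3. Effect on power.** Let q be the share of each arm entering at 21 or more. The documents do not give q, so a range is assumed. Suppose that all of these patients score 21 or more again and that melatonin has no effect on them. Each arm's rate becomes q + (1−q)p, with p = 0.31 or 0.155. Power at 120 per arm is

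Φ{[d√120 − 1.96√(2p̄(1−p̄))] / √(p₁(1−p₁)+p₂(1−p₂))}, where d = p₁−p₂.

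| q | Placebo | Melatonin | Difference | Risk ratio | Power |
|---|---|---|---|---|---|
| 0 | 31.0% | 15.5% | 15.5 points | 0.50 | 82% |
| 2% | 32.4% | 17.2% | 15.2 points | 0.53 | 78% |
| 5% | 34.5% | 19.7% | 14.7 points | 0.57 | 73% |
| 10% | 37.9% | 24.0% | 14.0 points | 0.63 | 65% |

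For q = 5%: p̄ = 0.2709 and d = 0.14725, so (1.6130 − 1.96×0.6285)/0.6198 = 0.615, and Φ(0.615) = 0.73.

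**4. Relaxing the assumption.** At q = 5%, suppose instead that 80% of these patients on placebo and 60% on melatonin score 21 or more again (an illustration, not a figure from the documents). Placebo: 0.05×0.80 + 0.95×0.31 = 33.5%. Melatonin: 0.05×0.60 + 0.95×0.155 = 17.7%. Power is 80%, close to the undiluted 82%.

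**5. Restricting to baseline below 21.** If the remaining patients have 31% v 15.5%, q = 5% leaves 0.95×120 = 114 per arm and 79.5% power. q = 10% leaves 108 per arm and 77%.

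**The case against.** The case on the other side is substantial on size.

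- **The share is unknown.** The worked score shows that the route exists, not how often it is taken. The exclusions for known sleep disorder, chronic hypnotic use and previously treated depression narrow the route without closing it. This stands, and is why the power figures are a range.
- **The event is a later score.** A reader might infer that melatonin could not have prevented these events, or that they add the same number to both arms. The documents do not support either. A patient at 21 who drops to 20 and stays there is not an event, and sleep, one likely source of such scores, is something melatonin is meant to improve. What cannot be prevented is onset, because it precedes treatment. On the other hand, an endpoint met at any time after baseline gives several chances to score 21 or more, so persistence may be high.
- **No bias between arms.** Baseline status precedes treatment and is balanced on average by randomisation. A reader might infer a biased comparison or an inflated type I error, but neither follows.
- **The abstract is shorthand.** The eligibility section governs, so the abstract's wording alone proves little. The words used for the endpoint do suggest that only new cases are meant, but the stated definition does not enforce it.
- **An article may leave detail to the full protocol.** That does not answer the point. The article itself fixes the entry rule, the endpoint and the analysis population, and these do not fit together.

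**Conclusion.** The mismatch is real and lies in the definition of the primary endpoint. As written, patients already at the threshold can enter and be counted as new cases. The consequence is a mislabelled endpoint and a tendency to dilution, not bias.

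The loss of power is between almost nothing and the values tabulated: 82% down to 78%, 73% or 65% for shares of 2%, 5% or 10%. Those values assume that every such patient scores 21 or more again, that melatonin has no effect on them, and that 31% v 15.5% holds in the others. They should not be read as the expected loss. The eligibility of such a patient rests on one inference, up to 5 points per symptom.

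**What to change.** Before unblinding:

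1. Define an incident case as a post-baseline MDI total of 21 or more in a patient whose baseline total was below 21.
2. Prespecify the binary, log-rank and Cox analyses in randomised patients with a baseline total below 21. The baseline total is a pre-treatment variable, so the randomised comparison is kept.
3. Report these together with the analysis of all randomised patients, adjusted for baseline MDI total.
4. For patients still to be enrolled, reconcile the entry criterion with the endpoint threshold. Status of the trial reports 150 of 240 already included, so a change at entry alone cannot cover those patients. Steps 1 to 3 do.
5. Report how many patients in each arm entered at 21 or more.

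The cost is a few lines of text, since the MDI is already completed at baseline. The statistical price is a slightly smaller restricted set, with power just under the planned 80% at a 5% share and about 77% at 10%. Reporting the analysis of all randomised patients beside it keeps the intention-to-treat result in view.

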### Exploratory outcomes

The pattern of participants leaving the study before completion of the 12-week period will be investigated. The different reasons for leaving the study (e.g., withdrawal of consent, medicine compliance, recurrent ACS, etc.) will be compared between the two groups. Furthermore, the timing of dropout between the two groups will be compared.

Safety and potential side effects will be closely monitored during the entire trial and reported in the proceeding publication. For specifics, see the “Harms and adverse events” section.

The Hospital Anxiety and Depression Scale (HADS) was originally developed by Zigmond and Snaith in 1978 [50] with the purpose of developing an easy-to-use tool for screening for mood disorders in a hospital setting. In a cardiac setting HADS-D has been shown to have adequate internal consistency, reliability and construct validity [51].

Actigraphy is a noninvasive method used to objectively evaluate a patient’s sleep and circadian rhythm. An actigraph (Octagonal Basic Motionlogger, Ambulatory Monitoring Inc., Ardsley, NY, USA), which is a wrist-worn minicomputer, will be mounted on the participant’s nondominant wrist at enrollment and worn for 2–3 weeks until the first clinical visit. Actigraphy has been shown to have a high validity and accuracy compared to polysomnography (PSG), the “gold standard” of sleep evaluation [52]. Actigraphy has been used extensively in patients undergoing surgery [53] and in cancer patients [54] but has not been investigated thoroughly in post-ACS patients [20].

Subjective sleep outcomes will be evaluated using a sleep diary, visual analog scales (VAS), and the Pittsburgh Sleep Quality Index (PSQI). A sleep diary is the patient’s own account of sleep data, and the patient is asked to fill in a diary page each morning after awakening. Visual analog scales regarding sleep will also be assessed on the scale ranging from “best conceivable sleep” at 0 mm to “worst conceivable sleep” at 100 mm. Furthermore, patients will fill out VAS on general wellbeing, fatigue, pain and anxiety. Lastly, the patients will fill out the PSQI, which assesses sleep quality during the prior 4 weeks and has a clinically established cutoff of ≥5 as being a poor sleeper and ≥8 as having sleep problems needing treatment [55].

Blood analysis will analyze for circadian genotype *PER 3* which has a variable number tandem repeat (VNTR) polymorphisms (unique to primates) that consist of either a 4- or 5-U repeated coding region. *PER 3* has been associated with sleep disorders [56], affective disorders [57] and reduced cognitive function in relation to sleep deprivation [58]. We will investigate a possible relationship between circadian genotype (clock genes), sleep-wake cycle, and depressive symptoms following ACS.

### Participant timeline

A diagnosis of ACS is made by the attending physician according to relevant guidelines. Eligible participants (according to the inclusion and exclusion criteria) will be informed about the study by the clinical investigating team, and if possible, a later inclusion meeting will be planned. Hereby, the potential participants will receive adequate time to consider participation and the possibility of bringing an assessor. The participant will be presented to the study during their initial admission for ACS or at a later joint meeting during cardiac rehabilitation. A participant should be included within 4 weeks of their ACS. The participants’ flow through the study can be seen in the CONSORT flow diagram (Fig. 2) and the timing of outcome measurement in the SPIRIT figure (Fig. 3).

### Sample size

Sample size is calculated on the basis of a conservative assumption that 31% of patients following ACS will develop depressive symptoms [4] which we assume can be reduced to 15.5% by melatonin treatment. Power calculation is based on two-sided test and, with a power of 0.80 and a significance level of 5% (*α* = 0.05), the required sample size in each group is 116. There are no interim efficacy analyses planned. The patients will be randomized in blocks of 6 and, therefore, the study will proceed until 120 patients have been enrolled in each arm.

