## Background

By the year 2030 it has been anticipated that depressive disorder and ischemic heart disease will be the first and second leading causes of disability in developed nations, respectively [1]. Worldwide, an estimated 7 million people or more each year suffer from myocardial infarction (MI) [2]. In Denmark in 2011, the incidence rate of acute myocardial infarction was 553 cases/100,000 person-years, a prevalence of 4570 cases/100,000 persons, and a mortality of 123 cases/100,000 persons [3]. The prevalence of major depressive disorder following acute coronary syndrome (ACS) has been reported to be approximately 19.8% ((CI) 19.1% to 20.6%) assessed by structured clinical interviews [4]. However, the prevalence varies according to the tool used to evaluate depression [4–6], e.g., if the most frequently used self-report instrument, the Beck Depression Inventory (BDI), is used the prevalence is 31.1% ((CI) 29.2% to 33.0%) [4]. However, a prevalence as high as 50.5% has been reported with other questionnaires [5].

Depression following ACS has been associated with a 2.25 ((odds ratio), CI 1.73 to 2.93) increase in all-cause mortality, and a 2.71 ((odds ratio), CI 1.68 to 4.36) increase in cardiac mortality within 24 months of the primary event [7]. Depression was recently categorized by the American Heart Association (AHA) as an independent risk factor for adverse medical outcomes in patients after ACS [6]. Furthermore, the AHA has made recommendations for implementing screening for depression in the post-MI period [8].

Anxiety symptoms following ACS have not received as much attention as post-ACS depression [9]. A mix of both depressive and anxiety symptoms tend to coexist in patients following ACS [10] and they are found in up to 90% of depressed patients following MI [11]. The prevalence of anxiety symptoms varies from 24 to 37% among hospitalized MI patients [12, 13], and has been found to be associated with a 1.47-fold ((odds ratio), CI 1.02 to 2.13) increase in all-cause mortality [14]. However, a more recent meta-analysis could not confirm [15] this in post-ACS patients and the relationship was thought to be attenuated by comorbid depression. Anxiety symptoms have been shown to reduce heart rate variability [16], activate the hypothalamic-pituitary-adrenal axis [17], and enhance fibrin turnover [18]. Furthermore, anxiety is an independent predictor of cardiac events following MI [11, 19].

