## Discussion

The current manuscript describes a protocol for a primary prophylactic study targeting nondepressed patients following ACS. To the best of our knowledge, we are the first to investigate melatonin’s antidepressant, anxiolytic and hypnotic effects in this population.

The predominant focus of previous trials has been the treatment of depression in patients following ACS. A recent Danish study showed that 20% of patients following ACS have an incident depression and 67% of medical antidepressant treatment is made up of selective serotonin reuptake inhibitor (SSRIs) [65]. This is coherent with a systematic review describing the increased use of antidepressants (predominantly SSRIs) during the last three decades [66]. Awareness and treatment of depression following ACS has risen during the last decades; however, not much attention has been focused on preventive interventions.

We know of only one previous trial using a similar primary preventive strategy [67, 68], which showed an effect of prophylactic treatment with escitalopram (Cipralex) [67]. However, treating patients with a SSRI (SSRI before the onset of depression is not without risk. Treatment with SSRIs have been shown to be associated with sleep disturbances, sexual disturbances and arrhythmias [30]. Recently, specific concerns regarding the cardiotoxicity of citalopram (also escitalopram) have been raised [69]. There exists a dose-response relationship between citalopram and the prolonged QT interval syndrome which, in some cases, leads to sudden cardiac death. Furthermore, patients with a previous cardiac event (e.g., MI) constitute a high-risk population [69]. The DECARD trial [67] has, in light of this, been criticized for the unnecessary potential harm associated with SSRI treatment caused to nondepressed patients with a previous cardiac event. The premise of preventing the development of depressive symptoms in the specific population is, however, controversial. Any such intervention should, of course, have the highest degree of benefit and the lowest incidence of side effects.

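### The 80% power rests on a 31% prevalence of depression used as the incidence of new depressive symptoms in screened patients, and it is not a conservative input

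*Protocol article*

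**What the plan says.** The Sample size section of the protocol article sets the control rate: "Sample size is calculated on the basis of a conservative assumption that 31% of patients following ACS will develop depressive symptoms", "which we assume can be reduced to 15.5% by melatonin treatment". With a two-sided 5% test and power 0.80, "the required sample size in each group is 116". The number is then rounded up: "The patients will be randomized in blocks of 6 and, therefore, the study will proceed until 120 patients have been enrolled in each arm".

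Other sections bear on the 31%:

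- **Background** cites the same source and says that if "the Beck Depression Inventory (BDI), is used the prevalence is 31.1" per cent. Beside it stand 19.8% by structured interview (same source) and a highest value of 50.5% on other questionnaires.
- **Eligibility criteria** admit only patients with no "sign of current depression on the Major Depression Inventory (MDI) used as a diagnostic tool" at enrolment, up to 4 weeks after the event. Ongoing or previous drug-treated depression, known sleep disorder and chronic hypnotic use before the event are exclusions.
- **Primary outcome** is a new MDI score of 21 or more at any time after baseline, over the 12 weeks of follow-up.
- **Discussion** cites a Danish study in which "20% of patients following ACS have an incident depression".
- **Statistics** names Fisher's exact test and/or the chi-squared test for this comparison.

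**The concern.** A prevalence counts patients who are already depressed. This trial removes them at entry, together with anyone previously treated with drugs for depression, and then counts new cases only. The 31% therefore comes from a different population (all patients after acute coronary syndrome), a different measure (prevalence) and a different scale (Beck, not MDI). Nothing in the article links it to the 12-week incidence of MDI ≥21 in screened patients.

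The direction matters. When the relative effect is fixed at a halving, a higher control rate gives more power, so 31% is the favourable choice compared with 20%, not the cautious one. If the true rate is lower, a null result would be read against a claimed 80% power that the trial did not have.

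Attrition is a secondary issue. The step from 116 to 120 is explained by block size alone. The Interventions section lists several compulsory exits, and data collection stops when a patient leaves.

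**Working it through.** **1. The plan's own figure.** Inputs from Sample size: p1 = 0.31, p2 = 0.155, two-sided α = 0.05, power 0.80, 1:1. Pooled two-proportion formula:

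n = [1.96·√(2p̄(1−p̄)) + 0.842·√(p1(1−p1) + p2(1−p2))]² / (p1−p2)²

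- p̄ = (0.31 + 0.155)/2 = 0.2325, and 2p̄(1−p̄) = 0.3569
- p1(1−p1) + p2(1−p2) = 0.3449
- n = (1.171 + 0.494)² / 0.0240 = 115.4, rounded up to **116**

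The plan's number reproduces. At 120 per arm, power is 81.5% by the normal approximation and 82.1% by exact enumeration of the chi-squared test.

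**2. Power at 120 per arm when the control rate varies.** The relative halving is kept. Power is by exact enumeration of the uncorrected chi-squared test; the n needed is from the formula above. Apart from the plan's 31%, the control rates are assumptions; 20% is the value in the Discussion.

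| Control rate | Melatonin rate | Power at 120/arm | n/arm for 80% |
|---|---|---|---|
| 35% | 17.5% | 88% | 99 |
| 31% | 15.5% | 82% | 116 |
| 25% | 12.5% | 71% | 152 |
| 20% | 10% | 59% | 199 |
| 15% | 7.5% | 46% | 278 |

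Power reaches 80% at a control rate close to 30%, so there is little room below the design value. With Fisher's exact test, the other named test, power is 77.9% at 31% and 51.6% at 20%.

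**3. Detectable effect at a 20% control rate.** With 120 per arm, 80% power (normal approximation) needs about 7.6% on melatonin. That is a relative reduction of 1 − 7.6/20 = 62%, against the 50% assumed.

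**4. Attrition.** The margin over 116 is 4/120 = 3.3%. The article gives no expected loss, so 10% and 20% are assumptions. Treating lost patients as giving no information (exact chi-squared, risk halved):

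| Evaluable per arm | 31% v 15.5% | 20% v 10% |
|---|---|---|
| 120 (no loss) | 82% | 59% |
| 108 (10% loss) | 78% | 55% |
| 96 (20% loss) | 73% | 50% |

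At either control rate, a 20% loss costs about 9 points. Moving the control rate from 31% to 20% costs about 23. The event rate is the larger issue.

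**The case against.** The strongest reply is that the 20% is no better matched to the endpoint than the 31%. The Discussion gives it as incident depression, with no instrument, threshold or time window. The trial's event is a self-rated score, collected every 2 weeks, counted at any time, and including mild cases. The Abstract says that milder symptoms are more frequent than significant depression. The Background shows questionnaires giving higher rates than interviews, so 19.8% by interview is a weak benchmark. Eligibility uses the MDI diagnostic algorithm while the endpoint uses the total score, so patients with appreciable subthreshold scores can enter and later cross 21. The rate could thus exceed 20%, and even 31%, where power is above 80%. All of this stands.

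The attrition figures in the working are also pessimistic. Patients non-compliant before the first follow-up visit are replaced, multiple imputation is planned, data collected before leaving are kept, and patients withdrawn for depression will normally already have had the event. This stands too.

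A reader might infer that 240 patients do not deliver 80% power, or that the calculation is wrong. The documents support neither: the formula is right, and the rate that would settle the matter is not given. None of this turns a prevalence into an incidence, however. Nor does it rescue the word conservative: the only figure in the article well above 31% is the 50.5%, which is itself a prevalence.

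**Conclusion.** The point holds as a defect of input and description, not of arithmetic. The 116 per group is correct for 31% against 15.5%, but 31% is a prevalence on another scale, applied to new cases in patients screened to be non-depressed. Both the article's incidence figure (20%) and the interview prevalence from the same source (19.8%) lie below it, so it cannot be called conservative.

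The stated 80% is therefore unsupported rather than shown to be false. Over control rates of 15% to 35%, power at 120 per arm runs from 46% to 88%, and at 20% a true halving would be missed about 4 times in 10. These figures assume a constant relative halving, an uncorrected chi-squared test and no loss. Attrition is a lesser matter, and its size rests on assumed loss rates.

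**What to change.** In the Sample size section:

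- Delete the word conservative and describe 31% as an assumption based on a Beck prevalence.
- Restate power at 240 patients for control rates on both sides of 31%, for example 15% to 35%, with the detectable difference at each.
- Say that the step to 120 is block rounding and not a drop-out allowance. Show power under attrition rates labelled as assumptions, noting the replacement rule and the planned imputation.

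Optionally, before unblinding, tabulate the pooled rate of MDI ≥21 across both arms to place the trial within that range. The article reports 150 of 240 patients included. The design values imply a pooled rate of (31 + 15.5)/2 = 23.25%; a control rate of 20% with halving implies (20 + 10)/2 = 15%. Because the arms are not compared, this is not an interim efficacy analysis and spends no alpha.

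The cost is a change of text, a short table and, if wanted, one blinded count. No extra patients are proposed. The stated power will look less favourable over most of the range.
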